### Who will take informed consent? {26a}

The surgeon, [name], will recruit the patient when discussing the pancreatosplenectomy treatment with the patient. Patients from CPGH will be selected for treatment from August 2019 to 31 September 2022. The trial was consistent with the principles of the Declaration of Helsinki and in accordance with the Medical Research Involving Human Subjects Act (WMO), and has been approved by the medical ethics committee of CPGH. Data are processed anonymously to protect the participants’ privacy. Written informed consent for the study will be obtained from each patient before surgery.

### Additional consent provisions for collection and use of participant data and biological specimens {26b}

On the consent form, if the participant opts out of the trial, the participant is asked if he or she agrees that their data may be used. Participants will also be required to allow the research team to share relevant data with people from the university or relevant authorities.

## Interventions

### Explanation for the choice of comparators {6b}

Previous studies on RAMPS were conducted under laparotomy and laparoscopy. There is still a world-wide lack of clinical studies on the safety and clinical efficacy of robotic RAMPS. We intend to conduct an RCT to compare short-term surgical oncological outcomes of robotic RAMPS and robotic SRPS in patients undergoing distal pancreatectomy. Through this study we want to find out whether RAMPS performs better than SRPS in robotic surgery.

### Intervention description {11a}

#### Surgical technique

##### Robotic radical antegrade modular pancreatosplenectomy

All robotic distal pancreatectomy (RDP) procedures will be performed using the da Vinci™ Si Surgical System (Intuitive, Sunnyvale, CA, USA). Once general anesthesia has taken effect, the patient is placed in a supine position. Our surgical procedures of RDPS and LDPS have been described previously [16, 17]. The layout of the trocar is shown in Fig. 2 [17]. Diagnostic laparoscopy is performed to rule out metastasis. The gastric colon ligament is opened and the superior mesenteric vein is separated at the lower margin of the pancreatic neck. The little omentum capsule is then opened to dissect the common hepatic artery, and para-hepatic arterial lymph nodes are dissected (groups 8a and 8p). The gastroduodenal artery is isolated, and then the superior portal vein of the pancreas is exposed. The pancreatic neck tunnel is located and the pancreatic neck is disconnected. Lymph nodes around the celiac trunk (nine groups) and fibrous adipose tissue are dissected. The splenic artery is isolated along the celiac trunk, is ligated and severed at the root, and the left gastric artery is severed when necessary. The distal pancreas is pulled from right to left, the splenic vein is severed from the root, and the proximal end is closed with 5-0 prolene continuous suture. Lymph nodes are dissected downward from the celiac trunk and the periceliac nerve plexus to the superior mesenteric artery, and the left lymph node of the superior mesenteric artery is dissected (group 14c and group 14d). Dissection is continued posteriorly to reveal the leading edge of the left renal vein and left adrenal vein. The specimen is redirected to the left to ensure that the anatomical resection plane is located behind Gerota’s fascia. The anterior approach should be close to the left renal vein, renal capsule, and the front edge of the left adrenal surface to clear the retroperitoneal tissue (this is the anterior RAMPS). The posterior approach requires resection of the left adrenal gland and its surrounding tissue (posterior RAMPS). At the same time, the upper and lower edges of the pancreas are freed, and then the ligaments around the spleen are removed, and the specimen is finally removed.

**Fig. 2 Fig2:**
[figure not shown]
Robotic port placement for robotic distal pancreatectomy (RDP). C, 12-mm trocar for camera; A, 12-mm trocar for assistant instruments; 1, 8-mm trocar for right robotic arm; 2, 8-mm trocar for left robotic arm; 3, 8-mm trocar for the fourth robotic arm

##### Robotic standard retrograde pancreatosplenectomy

Anesthesia and positioning of the trocar are as described above for RAMPS. The colonic ligaments are opened and the spleen-stomach ligaments, splenic-colonic ligaments, and splenic-diaphragmatic ligaments are separated to free the spleen. The pancreas is separated from the retroperitoneum from left to right and is disconnected about 2 cm away from the distal end of the tumor. Then the pancreatic stump is sutured to stop the bleeding.

#### Intra-abdominal drainage

A drainage tube will be placed to assess the pancreatic fistula as the primary endpoint before the abdomen is closed. The number and location of the inserted drainage tubes will be recorded in the data sheet, and we will specify when to remove the drain.

### Criteria for discontinuing or modifying allocated interventions {11b}

#### The rejection and withdrawal criteria

The criteria for rejection and withdrawal are (1) the patient does not meet the inclusion criteria of the study; (2) the clinical data obtained after inclusion are incomplete, and further clinical statistical analysis cannot be conducted; (3) the patients experienced serious adverse events/reactions related to the treatment regimen, and the investigator considered it necessary to withdraw them from the trial; (4) during the trial, the patient’s condition continued to deteriorate and dangerous events might occur, so the researcher considered it necessary to withdraw the patient from the clinical trial; (5) patients who voluntarily withdrew during the trial - all patients who gave informed consent and were eligible to participate in the trial at screening, regardless of when or where they withdrew, were classified as dropouts: they did not complete the observation period specified in the agreement; and (6) poor treatment compliance affecting the determination of efficacy and safety.

### Strategies to improve adherence to interventions {11c}

#### Concurrent and supportive treatments

Adherence is not an issue for patients as this is a surgical trial. We will determine details of the operation postoperatively by checking the surgical record.

### Relevant concomitant care permitted or prohibited during the trial {11d}

The surgeon will determine the use of antibiotics, blood products, analgesics, H2 blockers, and proton pump inhibitors based on perioperative management. Octreotide will be routinely applied to prevent pancreatic fistula. Abdominal ultrasonography will be performed regularly to determine the presence of peritoneal effusion. The serum amylase and bilirubin will be measured regularly in the drainage fluid of the abdominal drainage tube after operation. Implementing robotic RAMPS or robotic SRPS will not require alteration to usual care pathways and these will continue in both trial arms.

### Provisions for post-trial care {30}

There is no anticipated harm or need for compensation due to trial participation.

### Outcomes {12}

#### Endpoints

The primary efficacy endpoint of the trial will be the rates of resection margins. In the case of malignant pancreatic disease, resection margins are classified by a margin to tumor distance ≥ 1 mm (R0), a margin to tumor distance < 1 mm (R1) or a macroscopically positive margin (R2) [18]. The secondary endpoints are (1) the number of harvested lymph nodes; (2) retrieval postoperative complications including pancreatic fistula, intra-abdominal abscess, and anastomotic leakage, according to the Clavien-Dindo classification (Table 1): complications classified as higher than grade II are regarded as clinically significant [19]; and (3) perioperative indicators; such as duration of the operation, blood loss, blood transfusion volume, rate of transition to open surgery, postoperative hospitalization days, and hospital costs.

**Table 1 Tab1:** Complication grades according to the Clavien-Dindo classication scheme

Grade	Definition
V	Death of patient
IV	Life-threatening complication. Requiring intensive care unit management
IVa	Single organ dysfunction
IVb	Multi-organ dysfunction
III	Requiring surgical, endoscopic, or radiological intervention
IIIa	Intervention not under general anesthesia
IIIb	Intervention under general anesthesia
II	Requiring pharmacological treatment with drugs other than those allowed for grade I complications
I	Any deviation from the normal postoperative course without the need for pharmacological treatment or surgical, endoscopic, and radiological intervention

### Participant timeline {13}

An independent research physician will not be involved in the treatment and monitoring of patients in the surgical room and enter all necessary data into the prepared clinical report form (CRF). The CRF will be completed as soon as possible, preferably on the day of the patient’s visit and treatment (Table 2). Reasonable explanations should be given for all missing data. The complete CRF page will be examined for completeness and reasonableness by the principal investigator (PI) and responsible supervisors.

**Table 2 Tab2:** Flow chart of the trial

	Screening					
	Visit 1 Before surgery	Visit 2 Day of surgery	Visit 3 POD 1	Visit 4 POD 3	Visit 5 POD 7	Visit 5 POD 30
Informed consent	x					
Personal data	x					
Physical examination	x					
Previous medical history	x					
Inclusion/exclusion criteria	x					
CT/MRI	x					
Blood tests	x		x	x	x	x
Trial intervention		x				
Intraoperative outcomes		x				
Complications		x				
Adverse events		x	x	x	x	x
Postoperative outcomes			x	x	x	x

*CT* computed tomography, *MRI* magnetic resonance imaging, *POD* postoperative day

### Sample size {14}

Determination of the marginal resection rate is the main endpoint of this study. Published reports describe an R0 resection rate of 50–74% in distal adenocarcinoma in studies with large sample sizes (*n* > 100 patients) [20, 21]. A systematic review of radical antegrade modular pancreatosplenectomy, which identified 13 observational studies involving 354 patients undergoing RAMPS, showed that the R0 resection rate was 88% [22]. According to these studies, we used a two-sided log-rank test, which requires about 23–123 patients in each group with 80% power at the 0.05 level of significance (NCSS and PASS 11 (NCSS Statistical Software, Kaysville, UT, USA)). Considering that there is a large gap in the estimated quantity of samples, we plan to collect 90 samples in each group. Considering a dropout rate of 10%, the total sample size required is 200 patients. After 50 samples have been collected in each group, we will make a mid-term comparison to determine whether there are significant differences between the groups. Based on the results, we decide whether or not to conduct further data collection.

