**Methods:**

This is a randomized, single-center clinical trial. All participants are adult patients with primary pancreatic cancer, who are undergoing RAMPS or SRPS. The primary endpoints are R0 rate (resection margins are classified by a margin to tumor distance ≥ 1 mm). The secondary endpoints are the number of harvested lymph nodes, perioperative complications and perioperative indicators (duration of surgery, blood loss, blood transfusion volume, costs).

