## Statistical methods

### Statistical methods for primary and secondary outcomes {20a}

Statistical analysts do not participate in clinical observation. They will be blinded to allocation and responsible for statistical analysis of research data and timely delivery of statistical reports to the research director. All analyses will be performed and reported in accordance with the Consolidated standards of reporting trials (CONSORT) statement and the ICH E9 “Statistical Principles in Clinical Trials”. Primary and secondary outcomes will be cross-checked against data. The measurement data are expressed as mean plus/minus standard deviation. The normality test and homogeneity test of variance will be performed first. The independent sample *t* test will be used to compare normally distributed continuous variables, and the values will be represented as the mean with standard deviation. Continuous non-normally distributed variables will be compared using the Mann-Whitney *U* test, and the values will be expressed as the median of the quartile spacing. The categorical variables are compared using the chi-square test or the Fisher’s exact test, and values will be expressed as proportions with corresponding risk ratios and 95% confidence intervals. *P* < 0.05 indicates statistical significance. Statistical analysis will be performed using SPSS 20.0 software.

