## Discussion

Trendelemburg completed the world’s first resection of the tail of the pancreas in 1882 [23]. Mayo standardized the procedure in 1913. In this way, the spleen was gradually removed from left to right, and the pancreas was gradually severed to remove the lesion [24]. But this type of surgery has disadvantages. During the process of resection, the tumor may be squeezed, causing metastasis or recurrence of the tumor.

In 2003, Strasberg modified the traditional method of pancreatic tail resection. The pancreatic neck was first separated and the superior mesenteric arteries and veins, splenic vessels, and celiac trunk were exposed. The corresponding lymph nodes were then dissected and the splenic vessels were severed. The tumor and spleen were finally resected from right to left. This operation mode can be in line with lymph node drainage mode to clean lymph nodes, and can achieve “no-touch” in the tumor resection, so as to improve the rate of tumor resection of R0 [5].

There have been some studies comparing the advantages and disadvantages of SRPS and RAMPS, suggesting that RAMPS is safe and feasible [25] and has a better R0 resection rate than traditional tail pancreatectomy (70–80%) [26]. In the system evaluation of Zhou in 2017, 13 clinical studies including 354 patients with RAMPS were included, and the R0 resection rate reached 88%, and the 5-year survival rate reached 37%. Compared with SRPS, RAMPS is associated with less bleeding, more lymph node dissection, and a higher R0 resection rate [22].

But there has been a lack of studies comparing the two approaches to robotic surgery. To evaluate the surgical and oncological outcomes of robotic RAMPS, we therefore will undertake a prospective RCT. This procedure may become a standard approach to robotic pancreatosplenectomy. In this way, the most beneficial technique can be selected for individual patients.

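### The sample size names a log-rank test for a yes/no margin endpoint, and the 90 per group then chosen has no stated power and falls short of 80% at the top of the plan's own control range

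*Protocol article*

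**What the plan says.** The abstract and the Endpoints section make the margin result the primary outcome: "The primary endpoints are R0 rate (resection margins are classified by a margin to tumor distance ≥ 1 mm"), and "The primary efficacy endpoint of the trial will be the rates of resection margins". A resection counts as R0 when the margin is at least 1 mm from the tumor.

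The Sample size section takes two literature inputs. For the comparator, "Published reports describe an R0 resection rate of 50–74% in distal adenocarcinoma"; for RAMPS, a systematic review "showed that the R0 resection rate was 88"%. It continues: "we used a two-sided log-rank test, which requires about 23–123 patients in each group with 80% power at the 0.05 level of significance". The size is then settled in one sentence: "Considering that there is a large gap in the estimated quantity of samples, we plan to collect 90 samples in each group". Adding 10% for dropout gives a total of 200.

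The statistical methods section names the analysis: "The categorical variables are compared using the chi-square test", with Fisher's exact test as the alternative. It plans no log-rank analysis.

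The Study setting section gives a different total, 256 patients randomized 1:1.

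**The concern.** A log-rank test compares times to an event. R0 status is read once from the specimen, so it has no event time and no censoring. If the size had really come from a log-rank calculation, it would not match the endpoint or the planned analysis, and 23–123 could not be relied on.

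The second problem is the step from that range to 90. The range is wide because the comparator rate is uncertain. The plan responds by taking a value inside it, without saying which comparator rate that value serves or what power it gives. The only power in the paragraph is the 80% attached to the range. A reader may carry it over to 90 per group, and a non-significant result might then be read as evidence against an R0 benefit. If the SRPS rate is at the top of the stated range, the trial would miss a true 14-point difference about one time in three.

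**Working it through.** **Inputs.** From the Sample size section: comparator R0 rate p₁ = 0.50 to 0.74, RAMPS rate p₂ = 0.88, two-sided α = 0.05, power 80%, 90 evaluable per group, 10% dropout. From Study setting: 1:1 allocation, total 256. The section does not label 50–74% as the SRPS rate; that it served as the control rate is inferred, and step 1 confirms it.

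**Step 1. Reproduce 23–123.** Two-proportion formula with pooled variance under the null and no continuity correction, where p̄ = (p₁ + p₂)/2:

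n per group = [1.960·√(2p̄(1−p̄)) + 0.842·√(p₁(1−p₁) + p₂(1−p₂))]² / (p₂ − p₁)²

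- 50% vs 88%: p̄ = 0.69; [1.960 × 0.6541 + 0.842 × 0.5963]² / 0.38² = 22.04, so 23.
- 74% vs 88%: p̄ = 0.81; [1.960 × 0.5548 + 0.842 × 0.5459]² / 0.14² = 122.07, so 123.

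Both match the plan exactly.

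**Step 2. Try a log-rank calculation.** Treat a margin that is not R0 as the event, with hazard ratio ln(0.88)/ln(p₁): 0.184 at 50% and 0.425 at 74%. The average event proportions are 0.31 and 0.19.

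- Schoenfeld: 11 and 43 events, so 18 and 114 per group.
- Freedman: 17 and 49 events, so 28 and 129 per group.

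Neither gives the pair 23 and 123.

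**Step 3. Power at 90 evaluable per group.** Inverting the same formula:

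power = Φ{[(p₂ − p₁)√n − 1.960·√(2p̄(1−p̄))] / √(p₁(1−p₁) + p₂(1−p₂))}

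At 74%: (0.14 × 9.487 − 1.0874)/0.5459 = 0.441, and Φ(0.441) = 67.0%.

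| SRPS R0 rate | Power vs 88%, 90 per group |
|---|---|
| 50% | >99.9% |
| 62% (midpoint) | 98.5% |
| 70% | 85% |
| 71.3% | 80% |
| 74% | 67% |

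Exact binomial enumeration at 74% gives 67.5% for the uncorrected chi-square test and 61.0% for Fisher's exact test.

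**Step 4. Other sizes at 74% vs 88%.**

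| Evaluable per group | Origin | Power |
|---|---|---|
| 100 | 200 in total, no dropout | 71.7% |
| 115 | 256/2 = 128, less 10% (128 × 0.9 = 115.2) | 77.6% |
| 123 | the plan's upper requirement | 80.3% |
| 128 | 256 in total, no dropout | 81.9% |

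**The case against.** Several points on the other side stand.

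- **The plan does not claim 80% power for 90 per group.** A reader might infer that it does, but the 80% belongs to the 23–123 calculation, and the text openly admits a large gap between the estimates. The supportable criticism is that the power of the chosen size is unstated, not that a stated power is false.
- **The log-rank label has no numerical effect.** Steps 1 and 2 show that the figures came from the right method, and the planned analysis is already suitable. It is an error of description.
- **The shortfall is at the edge of the range.** Control rates from 50% to 71.3% cover 21.3 of the 24 points, and 90 per group gives at least 80% power for all of them. Sizing inside a range of literature rates is a legitimate design judgement. What is missing is the assumption behind it.
- **The Discussion does not establish a control rate of 80%.** It says that RAMPS "has a better R0 resection rate than traditional tail pancreatectomy (70–80"%). A reader might take that figure as the traditional operation's rate and conclude that power could be as low as about 31% (80% vs 88%, 90 per group). The sentence is loosely worded and can also be read as the RAMPS rate, so that figure is conditional on one reading.
- **The total is not settled.** With 256 patients all evaluable, power at 74% would be about 82%. This does not repair the Sample size paragraph, which says 200, but it means that 67% applies only if 200 is the operative total.

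**Conclusion.** The concern holds in this form. The named test is wrong for the endpoint and did not produce the figures; the two-proportion chi-square calculation did. The chosen 90 per group is below the plan's own upper requirement of 123 and has no stated power. With 90 evaluable per group, power is at least 80% only up to an SRPS rate of about 71%, and falls to about 67% at 74% (about 61% with Fisher's exact test).

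This rests on 88% in the RAMPS arm, two-sided 0.05, 200 as the operative total, and dropout that leaves 90 per group. It does not show that the trial is underpowered over most of its stated range, nor that 90 is an indefensible choice.

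**What to change.** 1. In the Sample size section, replace 'two-sided log-rank test' with 'two-sided chi-square test for two proportions'.
2. State the power of the evaluable sample size across the plan's own 50–74% control range against 88%. For 90 per group: above 99.9% at 50%, 98.5% at 62%, 85% at 70%, 80% at about 71% and 67% at 74%. Say plainly that 80% is not reached above about 71%. Do not present 71% as the design assumption: no source in the document gives it, and it only follows from solving backwards from 90.
3. Reconcile the total of 200 with the 256 under Study setting, and give the power for the total that applies. If it is 256, power at 74% is about 82% with 128 evaluable per group, or about 78% with 115 after 10% dropout.
4. If an 80% control rate is mentioned (power about 31% with 90 per group), mark it as conditional on reading the Discussion's 70–80% as the traditional operation's rate.

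The cost is a rewritten paragraph and a less favourable stated power at the upper control rates. No added enrolment is asked for, and the planned analysis does not change.

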### Interim analyses {21b}

Statistical analysis will be performed when the total number of samples collected reaches 100. The primary investigator will obtain these interim results and decide whether to continue the experiment. We will discontinue the trial if the safety of the RAMPS surgery group is much lower than that of the control group in the outcome of the interim data.

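### The 100-patient look compares the groups for significance and governs accrual with no interim or adjusted final level; if R0 can be claimed at 0.05 at either look, type I error is about 8%, not 5%

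*Protocol article*

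**What the plan says.** Protocol article, Sample size {14}: the resection margin rate is the main endpoint, and the trial is sized "with 80% power at the 0.05 level of significance". The plan is 90 patients per group, or 200 in total after 10% dropout. The same paragraph then says that after 50 patients per group "we will make a mid-term comparison to determine whether there are significant differences between the groups". It adds: "Based on the results, we decide whether or not to conduct further data collection".

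Statistical methods {20a} gives one threshold for the analyses: P < "0.05 indicates statistical significance". Categorical variables are to be compared by the chi-square test or Fisher's exact test.

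Interim analyses {21b} places an analysis at 100 patients in total, which is the same look. The primary investigator receives the results and decides whether to go on. One reason to stop is named: "We will discontinue the trial if the safety of the RAMPS surgery group is much lower than that of the control group". No numerical boundary is given.

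Study setting {9} gives a total of 256 patients, so the size of the final analysis is itself unsettled.

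**The concern.** The sample size section states a decision rule: compare the groups for significance at 50 per group, then use the answer to continue or stop accrual. It stands in the paragraph that sizes the trial for R0, and 0.05 is the only level to apply. If R0 is the variable compared and a significant result ends the trial as a positive finding, the trial has two chances to succeed at 0.05, and the 5% used in the design is not kept.

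Two things are at stake. The false-positive rate for the primary endpoint would be higher than stated. A trial that stops early because it crossed a lenient threshold also tends to overstate the effect, here the gain in R0 rate. The interim section does not remove the problem, because it neither excludes R0 from the look nor sets a level for it.

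**Working it through.** **Inputs.** All are from the protocol: two-sided 0.05, 80% power, SRPS R0 rate 50–74% and RAMPS R0 rate 88% (Sample size {14}); look at 50 per group (Sample size {14}), 100 in total (Interim analyses {21b}); final N 180 evaluable or 200 randomised (Sample size {14}) or 256 (Study setting {9}); 1:1 allocation.

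**1. The plan's own figure.** For two proportions with pooled variance under the null and no continuity correction,

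n per group = [1.960·√(2p̄(1−p̄)) + 0.842·√(p₁(1−p₁)+p₂(1−p₂))]² / (p₂−p₁)².

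- 50% vs 88%: 22.04, rounded up to 23.
- 74% vs 88%: 122.07, rounded up to 123.
- 90/(1−0.10) = 100 per group, 200 in total.

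These match the stated 23–123 and 200. The range is therefore a fixed-sample calculation with one test at 0.05 and contains no allowance for an interim look. (The protocol calls the test log-rank. That is a separate matter and does not affect this point.)

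**2. Type I error of two looks at 0.05.** Under the null, the interim and final statistics Z₁ and Z₂ are approximately bivariate normal with correlation √(100/N). The overall error is 1 − P(|Z₁| < 1.96 and |Z₂| < 1.96).

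| Final N | Information at look | Overall two-sided error |
|---|---|---|
| 180 | 100/180 = 0.556 | 1 − 0.9188 = 0.0812 |
| 200 | 100/200 = 0.500 | 0.0831 |
| 256 | 100/256 = 0.391 | 0.0866 |

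**3. Check on binary data.** In 1,000,000 simulated trials per scenario, with 50 then 90 per arm and common R0 rates of 62–88%, an uncorrected chi-square test at both looks gives 8.1–8.4%. Fisher's exact test at both looks gives 4.4–5.6% overall, against 3.1–3.7% for a single final Fisher test. The second look still adds error there, but the starting point is conservative.

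**4. Effect of stopping early.** With true rates of 74% and 88%, about 45% of simulated trials cross 0.05 (uncorrected chi-square) at 50 per group. The mean observed difference among them is 20.7 percentage points, against a true 14.

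**5. Boundaries that hold 5%.** O'Brien-Fleming-type spending, 0.025 per side, gives an interim two-sided level of 4·[1 − Φ(2.241/√t)]. The final level is then solved so that the total is 0.05.

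| Final N | Interim p | Final p |
|---|---|---|
| 180 | 0.0053 | 0.0483 |
| 200 | 0.0031 | 0.0490 |
| 256 | 0.0007 | 0.0498 |

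A level of 0.001 at the look followed by 0.05 at the end gives a total of 0.0502 for N = 180.

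**6. Cost in power.** At 74% vs 88% with 90 per group, a single final test at 0.05 has simulated power 67.5%. The 0.0053/0.0483 boundary gives essentially the same (67.6%).

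**The case against.** Three parts of the opposing case stand and limit the point.

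First, the protocol does not print 0.05 beside the look. A reader might conclude that it explicitly tests at 0.05 twice. It does not. That 0.05 applies at the look is an inference: the look seeks significant differences, and the document defines significance only once. Interim boundaries are often left to an analysis plan or monitoring charter not shown here. But an unseen boundary would not change the published rule that ties continuation to significance, nor align the two sections.

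Second, the decision rule is open. It does not name R0, and it does not say that significance stops the trial with a positive claim. It follows a remark on the wide range of estimated sample sizes, so it could mean a check on whether more patients are needed, or a stop for lack of difference. A stop for lack of difference would not inflate type I error. Nor would a look confined to safety. The 8% is therefore conditional.

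Third, a reader might infer that the interim section makes the look safety-only and so flatly contradicts the sample size section. The text does not support that. It first leaves continuation to the primary investigator without restriction and then names one safety reason. It neither says that safety is the only reason nor excludes R0. The sections are unaligned rather than plainly opposed.

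The choice of test also matters. With Fisher's exact test throughout, the overall error stays near 5%. However, at common R0 rates of 62–88% with 50 per group, the smallest expected cell count is 50 × 0.12 = 6, so the uncorrected chi-square test is the likelier choice.

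**Conclusion.** The point holds in conditional form. The protocol states a significance comparison that governs accrual, offers only one level (0.05), and neither sets an interim or adjusted final level nor allows for the look in the sample size. Its two descriptions of the look do not settle whether R0 can end the trial.

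The size of about 8.1–8.7%, depending on which final N is used, rests on three assumptions: a significant R0 result at the look can be claimed as positive, 0.05 applies both there and at the end, and the test is the uncorrected chi-square. Under them, false positives are about 1.6 to 1.7 times the stated rate (8.1/5 to 8.7/5), and trials that stop at the look overstate the R0 gain by about half (21 against 14 points at the assumed rates). The documents do not support an unconditional statement that the trial's false-positive rate is 8%.

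**What to change.** Reconcile Sample size {14} and Interim analyses {21b} before the 100-patient look; afterwards the choice could be influenced by the data. Either of these is sound:

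- State that R0 is not tested for stopping at the look, and keep 0.05 for the final analysis.
- State a group-sequential boundary for R0. For 100 of 180 patients, examples are two-sided p < 0.0053 at the look and p < 0.048 at the end, or p < 0.001 and then 0.05 (total 0.0502).

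If a boundary is chosen, recompute it once the final N is settled among 180, 200 and 256. In either case, state that a non-significant result at the look does not change the final sample size.

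The cost is one paragraph of amendment. The first option loses no power, and the spending boundary loses less than 1 percentage point.
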